#### Analysis of the clinical relevance of the outcome changes

To examine whether the changes observed in depressive symptoms are clinically significant, the percentage of participants whose depression remits according to the MINI at the end of treatment will be compared between the two groups, using two Cochran-Mantel-Haenszel tests (one for the results obtained after the intervention and another for the results obtained after follow-up). In addition, changes in depressive symptoms in terms of response to treatment will be analyzed. That is, we will compare the percentage of patients who experience a reduction of at least 50% in the severity of depressive symptoms at the end of the treatment with the percentage of patients who do not respond to treatment [8] using the Cochran-Mantel-Haenszel test. To examine whether changes in pain intensity are clinically significant, we will compare the percentage of women responding to treatment in terms of the intensity of pain at the end of treatment with the percentage of women not responding to treatment using the Cochran-Mantel-Haenszel test. Treatment response will be defined as reductions of at least 2 units on the pain scale from 0 to 10, as this is the criteria usually employed for clinically significant pain improvement [40].

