### Randomization

Participants who meet all the inclusion criteria after the eligibility interview will be randomized to the two arms, with a 1:1 allocation ratio. We plan to randomize every time we are able to recruit enough participants for a treatment group and a control group. That is, randomization will take place with 16 participants each time, eight of them being assigned to the experimental arm and the other eight to the control. Nonetheless, due to recruitment and logistics issues, it is possible that sometimes a smaller or bigger group of participants needs to be randomized into the two arms. Randomization will be conducted by an independent researcher (not involved in the assessments, treatment, or data analysis). The project coordinator will submit an email to this independent researcher with the ID numbers of participants to be randomized. This researcher will use a computer program to randomly assign participants to the control and the experimental groups. The researcher will then submit a pdf file to the research coordinator with the assignment and will keep a copy for record. The project coordinator will be the only person from the team who is aware of participant allocation, and will keep this information in a file in her computer protected with a password. The principal investigator, co-investigators, and statistician will be blind to participant allocation. The project coordinator will then contact participants to inform them about the initiation of treatment. Notably, all participants will receive the BA intervention at some point. The only difference between the experimental and control groups will be that the former will receive treatment before participants in the control group. To minimize bias, all participants will be informed that they will wait before receiving the intervention and that they will be assessed periodically until their treatment begins, but they will not be aware of how long they or the other people in the study will have to wait. They will also be informed that nobody will wait more than 6 months.

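### The two response analyses are worded as responders against non-responders instead of BA plus usual care against usual care, and the Cochran-Mantel-Haenszel tests name no stratum although women are randomized in batches

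*Protocol article*

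**What the plan says.** The protocol article's section headed Analysis of the clinical relevance of the outcome changes sets out three kinds of binary comparison, all by the Cochran-Mantel-Haenszel (CMH) test.

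- **Remission (MINI).** The percentages "will be compared between the two groups, using two Cochran-Mantel-Haenszel tests", one after treatment and one after follow-up. The arms are named.
- **Depression response.** The criterion is a "reduction of at least 50% in the severity of depressive symptoms". The percentage meeting it is to be compared "with the percentage of patients who do not respond to treatment [8] using the Cochran-Mantel-Haenszel test". No arm is named.
- **Pain response.** The criterion is "reductions of at least 2 units on the pain scale from 0 to 10". The percentage of women responding is to be compared "with the percentage of women not responding to treatment using the Cochran-Mantel-Haenszel test". No arm is named.

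No stratifying variable is given for any of these tests.

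The Randomization section describes a batch design: "We plan to randomize every time we are able to recruit enough participants for a treatment group and a control group". The plan is that "randomization will take place with 16 participants each time", eight to each arm, although "it is possible that sometimes a smaller or bigger group of participants needs to be randomized into the two arms". The Data analyses section describes a two-level hierarchical linear model (HLM), within and between subjects, with covariates added when they differ significantly at baseline. Batch does not appear as a stratum, level or covariate anywhere in the Analytic plan.

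**The concern.** Two of the prespecified analyses that are meant to show clinical benefit are given the wrong contrast. The percentage responding and the percentage not responding are complements, so setting one against the other says how common response is in the whole sample. It does not say whether response is more common with BA. The abstract expects effects that are clinically as well as statistically significant, and these analyses are meant to support the clinical part. The wording occurs twice, directly after a remission sentence that is worded correctly, so it should be corrected before the analysis is run.

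The second, smaller matter is the choice of test. A CMH test is used to combine a comparison over strata. The article fixes that test, gives no strata, and describes a randomization that supplies a natural one, the batch. Between-batch differences over the recruitment period then stay in the error term, at some cost in power.

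**Working it through.** The article gives no response rates, no batch variance and no figure for these tests, so there is no stated value to reproduce. The N = 90 and power of .80 in the sample size section concern the HLM, not these comparisons. Every response rate and batch effect below is an assumption for illustration.

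**1. What each contrast measures.** Let p1 and p0 be the response rates in the two arms, with 45 women in each.

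- Arm contrast: p1 − p0.
- Contrast as worded: r − (1 − r) = 2r − 1, where r = (p1 + p0)/2. It is zero when r = 50%, whatever p1 − p0 is.

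**2. Same total, different treatment effects.** With 45 responders in 90, 2r − 1 = 0 in every row.

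| Responders BA+UC / UC | Pearson chi-square | p (arm contrast) |
|---|---|---|
| 22/45 vs 23/45 | 0.044 | 0.83 |
| 29/45 vs 16/45 | 7.51 | 0.006 |
| 36/45 vs 9/45 | 32.4 | about 1e-8 |

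Check of the middle row: difference = 13/45 = 0.289; standard error = √(0.5 × 0.5 × 2/45) = 0.1054; z = 2.74; z² = 7.51.

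The converse also occurs. With 14/45 in each arm there is no treatment effect (p = 1), yet 28/90 = 31% responding against 62/90 = 69% not responding is a marked imbalance.

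**3. How far an arm-free reading could mislead.** If the wording were turned into an exact binomial test of r = 50%, a test the article does not name, simulation (20,000 runs, 45 per arm) gives:

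| True rates | Rejects, arm-free reading | Rejects, arm comparison (Pearson) |
|---|---|---|
| 30% vs 30% | 97% | 5% |
| 50% vs 50% | 4% | 4.5% |
| 65% vs 35% | 4% | 81.5% |
| 70% vs 30% | 3% | 97% |

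This shows that the two contrasts answer different questions. It does not predict what the trial's analyst would do.

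**4. CMH with one stratum.** The statistic is Pearson chi-square × (N − 1)/N = Pearson × 89/90. For 29 vs 16 it is 7.51 × 89/90 = 7.43, p = 0.006. It is a valid arm comparison that adjusts for nothing.

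**5. Stratifying by batch.** 90/16 = 5.6, so about six batches, simulated as five of 16 and one of 10, split 1:1 within batch.

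| Assumed batch SD (logit scale) | Type I error at 30%: stratified / one stratum | Power at 50% vs 20%: stratified / one stratum |
|---|---|---|
| 0 | 0.050 / 0.050 | 0.864 / 0.861 |
| 0.5 | 0.051 / 0.044 | 0.851 / 0.835 |
| 1 | 0.052 / 0.035 | 0.799 / 0.742 |

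Leaving batch out does not inflate type I error. It costs between nothing and about 6 percentage points of power over this range.

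**The case against.** The strongest objection is that a CMH test cannot be run on one pooled percentage. It needs a second variable, and the context supplies arm: the same paragraph opens with remission compared between the groups, and the design overview says that comparing the two groups is what establishes the benefit of adding BA. This stands. A reader might infer that the response analyses will carry no information on treatment, or that the trial will report false positives at the rates in the third step. The documents do not support that inference, because those rates come from a binomial test that the article does not specify. What remains is that the contrast as written is wrong in two places and is left for the analyst to repair.

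A second objection is that a journal article may leave strata to the full protocol or analysis plan, and that batching is described as logistics, not as a stratification factor. Taken alone, the missing stratum would not be an error. It is worth raising with the wording correction because the article fixes a stratified test while its own design offers an unused stratum.

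A third objection is that batch need not enter the HLM. This also stands. The Data analyses section tests whether the change parameter varies by treatment group, so treatment acts on the slope. A batch term on the intercept alone would not generally tighten that estimate. A reader might infer that the primary analysis is flawed without batch, but its arm comparison is valid as described.

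**Conclusion.** The point holds as a wording error of limited reach. The PHQ-9 response and pain response sentences state a contrast that does not measure the treatment effect and must be corrected; an arm comparison was probably meant. The remission comparison names the right contrast, and the primary HLM is not affected.

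The absent stratum is a lesser matter. A single-stratum CMH test is valid, and somewhat conservative if batches differ. The possible gain from stratifying, up to about 6 points of power, rests on an assumed batch SD of up to 1 on the logit scale, on assumed response rates of 50% and 20%, and on the planned batch sizes. With no batch effect the gain is essentially nil.

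**What to change.** Reword both response sentences along these lines: the proportion of responders will be compared between BA plus usual care and usual care by a Cochran-Mantel-Haenszel test stratified by randomization batch. Use the same stratum for the two remission tests. Say in advance how very small batches will be merged, since batch size may vary. If no stratum is intended, name a plain chi-square or Fisher test instead.

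A batch term in the HLM is optional. If one is added, it should act on the slope as well as the intercept, and its benefit depends on a batch variance that the article does not give.

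The cost is a change of wording. Batch can be recovered from the allocation files that the independent researcher keeps, so no new data are needed. The downside is a handful of strata, and little or no gain if batches turn out alike.

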#### Missing data

Participants who are retained throughout the follow-up will be compared with those who drop out from the study in terms of socio-demographic and clinical variables. Any significant difference between groups will be considered in the interpretation of results. As mentioned before, HLM will be conducted for group comparison. These analyses will use maximum likelihood estimation with robust standard errors for variables that are not normally distributed. This estimator has been shown to be robust in estimating missing data [41].

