### Analytic plan

#### Data analyses

In order to test whether there are differences between the two groups in the sociodemographic and clinical characteristics assessed at baseline, Student’s *t* tests will be performed for continuous variables and chi-square tests for categorical variables. If there are small or empty cells in the categorical tests, the chi-square test will be replaced by a Fisher’s Exact Test. Those variables in which statistically significant differences are found will be introduced in the analyses as covariates.

In order to examine differences between groups in the reduction of the primary and secondary outcome, HLM will be performed using MPlus. This analysis involves two levels of analysis: within-subject (level 1, which analyzes the change of subjects over time) and between-subject (level 2, through which the effect of treatment is examined). Repeated measures of symptoms are nested in each subject, and the analysis allows for estimating a change parameter along repeated measurements. The analysis tests whether the change parameter varies according to the treatment group, and other covariates. HLM allows one to consider in the analyses all participants (including those who drop out from the study). Therefore, these analyses will be conducted according to the principle of intention to treat. Finally, in order to test whether the decreases found after the follow-up in the pain-related variables are mediated by the decrease in depressive symptom severity, mediation analysis with bootstrapping will be conducted [39].

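### Baseline predictors of dropout have no stated route into the HLM, and the missing-data justification credits the estimator instead of stating missing at random

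*Protocol article*

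**What the plan says.** Three statements in the protocol article's Analytic plan matter here.

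- **Missing data, the dropout comparison.** "Participants who are retained throughout the follow-up will be compared with those who drop out from the study in terms of socio-demographic and clinical variables". The stated consequence is "Any significant difference between groups will be considered in the interpretation of results".
- **Missing data, the estimator.** "These analyses will use maximum likelihood estimation with robust standard errors for variables that are not normally distributed", followed by "This estimator has been shown to be robust in estimating missing data". The section states no assumption about why data are missing.
- **Data analyses, the covariate rule.** After baseline tests between arms, "Those variables in which statistically significant differences are found will be introduced in the analyses as covariates". The same section says "HLM allows one to consider in the analyses all participants (including those who drop out from the study" and derives the intention-to-treat label from that.

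The Data collection section adds that outcomes are taken by telephone at four time points, that women who leave the intervention are still contacted for assessment, and that each assessment is compensated.

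**The concern.** The two rules do not meet. One looks for variables that separate dropouts from retained women but gives them no role in estimation. The other admits variables to the model on a different criterion, imbalance between arms, which randomisation tends to prevent. A variable that predicts dropout and also predicts the PHQ-9 trajectory can pass through both and never enter the likelihood.

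This matters because likelihood inference may ignore the missingness mechanism only if missingness depends on data inside the model. Discussing a dropout predictor afterwards does not change the estimate. During the assessed period only one arm attends group sessions (10 over 2 months), so it is plausible that pain or function relates to dropout differently in the two arms. At stake is the treatment contrast for the primary outcome, and a stated justification that would lead a reader to think the matter is settled by the choice of estimator.

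**Working it through.** **No figure in the plan to reproduce.** The article gives no expected dropout rate and no missing-data calculation. Its N = 90 for power .80 could not be pinned down, because time scores, sidedness and treatment coding are not given (two-sided power ran from 0.24 to 0.995 across readings). The present point does not depend on it.

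**Step 1. The route into the model.** Take a baseline variable X that is balanced between arms and predicts dropout.
- Data analyses: no significant difference between arms, so X is not entered as a covariate.
- Missing data: a significant difference between dropouts and retained women, so X is discussed.
- Result: X has been identified and is still outside the likelihood.

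**Step 2. The screen itself.** Assume 18 of 90 women drop out. A two-sided 5% t test of 18 against 72 has 47% power for a 0.5 SD baseline difference and 20% for 0.3 SD. With 14 to 27 dropouts, power for 0.5 SD is 40% to 58%. The screen will often miss real predictors.

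**Step 3. Does leaving X out bias the contrast?**

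Inputs from Sample size calculation: intercept and slope variances 1, correlation −0.4, average slope −0.5, treatment effect on slope of size 0.45 (negative here, meaning a larger fall), covariate effect on slope 0.1. Assumed: residual variance 1, effects of X of 0.3 and 0.5 as well as 0.1, the dropout rates and the dropout mechanisms.

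Model: score at time t = intercept + slope × t + error, with slope = −0.5 − 0.45 × arm + g × X + random part. A linear growth model was fitted by maximum likelihood to very large samples (200,000 to 400,000), with and without X. Bias = estimate without X minus estimate with X.

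At about 15–20% dropout:

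| X and dropout | g | Without X | With X | Bias | Bias / 0.45 |
|---|---|---|---|---|---|
| Same link in both arms | 0.1 | −0.453 | −0.452 | −0.001 | 0.2% |
| | 0.3 | −0.454 | −0.452 | −0.002 | 0.4% |
| | 0.5 | −0.455 | −0.452 | −0.003 | 0.7% |
| Link in the treated arm only | 0.1 | −0.464 | −0.452 | −0.012 | 3% |
| | 0.3 | −0.487 | −0.452 | −0.035 | 8% |
| | 0.5 | −0.509 | −0.452 | −0.057 | 13% |
| Opposite links by arm | 0.1 | −0.476 | −0.453 | −0.023 | 5% |
| | 0.3 | −0.522 | −0.453 | −0.069 | 15% |
| | 0.5 | −0.565 | −0.453 | −0.112 | 25% |

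At the plan's own covariate effect of 0.1, the bias in the two differential cases is therefore 0.012 to 0.023. At 34–38% dropout, the differential cases ran from 0.474 − 0.449 = 0.025 to 0.675 − 0.452 = 0.223.

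The sign in the table follows from the chosen direction, in which women with the worse trajectory leave the treated arm. Reversing the link, or placing it in the control arm, reverses the sign.

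**Step 4. What the model already handles.** Without X, dropout that depended on arm alone (49% against 27%) gave −0.450. Dropout that depended on observed scores gave −0.449 to −0.455. Neither is a material bias.

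**Step 5. Against sampling error.** In 300 simulated trials of N = 90, the SD of the estimate was about 0.26. The largest bias at 15–20% dropout is 0.112 / 0.26 = 0.43 of a standard error; the smallest differential one is 0.012 / 0.26 = 0.05.

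**Step 6. Limit of the remedy.** Where X also modified the treatment effect (38% dropout in each arm), the estimate was −0.494 without X and −0.496 with a main-effect term. A main effect does not remove that bias.

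**The case against.** The strongest reply has four parts.

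- **The method is sound.** The likelihood part of the estimator uses incomplete records validly under missing at random, and baseline and earlier PHQ-9 scores are in the model. This stands, and it is why dropout related to observed PHQ-9 is not a problem. It does not rescue the sentence, which credits the estimator and omits the condition that makes it valid.
- **Missing outcomes may be few.** Leaving the sessions is not the same as missing an assessment. Contact continues by telephone with compensation. This stands and reduces the likely size.
- **The text does not forbid more.** Data analyses mentions other covariates, and the sample size calculation includes two that are not named. A fuller plan could add auxiliary variables or a sensitivity analysis. Their absence from an article is not the finding. The finding is that the two rules that are stated leave a known dropout predictor outside the model.
- **The bias is small.** At the assumed 15–20% dropout it is below one standard error. This stands and limits the weight of the point.

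Three stronger readings are tempting and unsupported. A reader might infer that bias will occur; it requires that X predict the trajectory beyond observed PHQ-9 and either relate to dropout differently by arm or modify the treatment effect. A reader might infer that it favours behavioral activation; the article gives no dropout rate or direction, and control women, who are waiting for treatment, may leave too. A reader might infer that the responder comparisons, set up "with the percentage of patients who do not respond to treatment [8] using the Cochran-Mantel-Haenszel test", use observed cases only; that section gives no denominator or missing-data rule, and the intention-to-treat label is attached to the HLM, not to these tests.

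**Conclusion.** The point holds as a possible and cheaply avoidable bias together with a wrong justification. As stated, the plan can identify a baseline predictor of dropout and leave it out of the primary model, and the arm contrast could then be biased in either direction if that predictor's link to dropout differs by arm.

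The size is modest: 3–25% of a slope effect of 0.45 at an assumed 15–20% dropout, always less than half a standard error at N = 90, and near zero when the link to dropout is the same in both arms and X does not modify the treatment effect. These figures rest on assumed dropout rates, mechanisms and covariate effects, and on a linear growth model.

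The criticism of the robustness sentence needs no such assumptions: robust standard errors deal with non-normality, and validity with missing data depends on missing at random given the modelled variables.

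**What to change.** 1. Replace the rule on dropout differences. Prespecify baseline pain intensity, FIQ-R, PCS and age, all within what the trial already collects, as covariates or auxiliary variables in the Mplus model, whether or not any between-arm or dropout test is significant. Session attendance should not be among them: it arises after randomisation and, during the comparison, exists in one arm only.
2. Replace the robustness sentence with an explicit statement that the analysis assumes data are missing at random given arm, observed scores and the prespecified baseline variables. Keep the robust standard errors, described as protection against non-normality.
3. Add one sensitivity analysis under missing not at random that shifts the unobserved PHQ-9 scores by a fixed amount. This also covers some of what item 1 cannot repair, such as a dropout predictor that modifies the treatment effect.

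The cost is plan wording, a few more lines of Mplus code, a slightly larger model at N = 90 and one more table. No new data are needed.

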## Discussion

Despite preliminary evidence suggesting that BA could be particularly suitable for treating depression among patients with fibromyalgia – as it addresses factors that seem to play a key role in the etiology of both disorders [6, 11–13] – to our knowledge, no studies have been conducted to examine the efficacy of this intervention in reducing depressive symptoms among these patients. This is important, as fibromyalgia and depression are highly coexistent and the interaction of both disorders leads to a worse prognosis. This is the first study in which the efficacy of BA in patients with fibromyalgia and major depression will be examined.

There are some limitations to the study design. First, all the instruments employed are self-report scales. Second, the follow-up assessment will take place at 3 months and studies with longer follow-up must be conducted in order to know whether the effects of the treatment are maintained in the long term. Third, participants under treatment with an antidepressant other than duloxetine will be excluded and, therefore, our results may not generalize to these participants. Nonetheless, requiring all subjects to be receiving duloxetine makes the sample more homogeneous, which is important in randomized clinical trials. Furthermore, as all participants will present with depression despite being under treatment with duloxetine, they will be considered unresponsive to duloxetine treatment. Thus, if we find that adding BA to UC reduces depressive symptoms, this can be interpreted as evidence that BA may be useful for patients who are refractory to duloxetine treatment. Finally, complete blinding of subjects is impossible given the type of intervention and fibromyalgia. Nevertheless, in this study all participants will receive the BA intervention at some point. The experimental and control groups will only differ in that the former will receive treatment before participants in the control group. As such, all participants will know that they will have to wait to receive the intervention, but they will not be given precise information about how long they will have to wait to receive it. Thus, they will not be aware of whether they are in the experimental group or in the control group. Finally, patients are known to be susceptible to placebo effect regarding pain [42], so future studies in which the effect of adding BA to UC is compared with the effect of adding an active intervention for depression to UC are still needed.

The results of this study should contribute to facilitate the integrated treatment of fibromyalgia and depression, and to reduce the burden to which health systems are exposed due to the lack of effective therapeutic strategies to treat these co-occurring conditions. In addition, we expect that our study contributes to the dissemination of evidence-based treatment, such as BA, among primary care professionals in Latin American countries. Our findings will also help to better understand the relationship between depression and pain. Finally, because BA will be applied in a group setting, our results will add support to the efficacy of BA in group format.

